## Abstract

**Background:**

Resources in any healthcare systems are scarce relative to need and therefore choices need to be made which often involve difficult decisions about the best allocation of these resources. One pragmatic and robust tool to aid resource allocation is Programme Budgeting and Marginal Analysis (PBMA), but there is mixed evidence on its uptake and effectiveness. Furthermore, there is also no evidence on the incorporation of the preferences of a large and representative sample of the general public into such a process. The study therefore aims to undertake, evaluate and refine a PBMA process within the exemplar of NHS dentistry in England whilst also using an established methodology (Willingness to Pay (WTP)) to systematically gather views from a representative sample of the public.

**Methods:**

Stakeholders including service buyers (commissioners), dentists, dental public health representatives and patient representatives will be recruited to participate in a PBMA process involving defining current spend, agreeing criteria to judge services/interventions, defining areas for investment and disinvestment, rating these areas against the criteria and making final recommendations. The process will be refined based on participatory action research principles and evaluated through semi-structured interviews, focus groups and observation of the process by the research team. In parallel a representative sample of English adults will be recruited to complete a series of four surveys including WTP valuations of programmes being considered by the PBMA panel. In addition a methodological experiment comparing two ways of eliciting WTP will be undertaken.

**Discussion:**

The project will allow the PBMA process and particularly the use of WTP within it to be investigated and developed. There will be challenges around engagement with the task by the panel undertaking it and with the outputs by stakeholders but careful relationship building will help to mitigate this. The large volume of data will be managed through careful segmenting of the analysis and the use of the well-established Framework approach to qualitative data analysis. WTP has various potential biases but the elicitation will be carefully designed to minimise these and some methodological investigation will take place.

**Electronic supplementary material:**

The online version of this article (10.1186/s12913-018-3302-8) contains supplementary material, which is available to authorized users.

## Background

In any healthcare system, the problem of scarcity exists, in that there are insufficient resources (such as monetary funds, staff time, estates space) to deliver all of the possible programmes and interventions [1]. Where resources are used to provide one service or intervention, there is an opportunity costs in terms of the benefit forgone by using these resources for an alternative service [2]. There is therefore a need to allocate resources in a way that meets the objectives of the health system, however these are defined [3]. This is often difficult as healthcare systems usually have complex and sometimes competing objectives.

Different healthcare systems have dealt with this need to undertake resource allocation in different ways, either explicitly or implicitly, with varying degrees of success in terms of maximising benefits. Methods of resource allocation are varied but do not usually address the opportunity costs associated with the decisions in a systematic way [3]. Examples of these methods include perpetuating historical allocations to different service areas and diverting funds to those areas where there is political, patient or clinician pressure (with those able to make their voice heard better placed to secure funds). A final example which also does not address opportunity cost would be allocating funds based on assessment of needs or defining core services. Methods developed in the field of health economics, such as cost-effectiveness and cost-utility analysis, have been used, but these address the performance of each intervention relative to cost and often do not actually address resource allocation issues. This usually results in multiple interventions being recommended with no consideration of the overall budget (i.e. where the resource will come from) or with only several alternatives being compared rather than holistically looking across a whole system [4]. A more pragmatic approach has been suggested which involves economics-based priority setting tools, an example of which is Programme Budgeting Marginal Analysis (PBMA) [5]. In this approach, the current spend in different areas is defined, areas for investment and disinvestment are identified and these are judged against criteria that are developed as part of the process to encapsulate benefit before recommendations on where to disinvest and where to invest are made.

In a review of PBMA applications between 1991 and 2009, although 65% had led to some change in actual resource allocation, ongoing use of PBMA after the academic study was achieved only in 22% of cases [6]. A further review of all explicit priority setting techniques between 2000 and 2017 echoed the lack of ongoing use and ascribed this to difficulties in the complexity and time burden of using the various frameworks [7].

Although the involvement of the public and the incorporation of their views in priority setting processes has been recognised as vital, typically only unrepresentative small groups of the public or single individuals have been involved in decisions. There have been only limited attempts in health to systematically elicit public preferences for use in commissioning decisions [8]. One particular economic tool, willingness to pay (WTP) could be used to systematically elicit of the views of a large sample of the public. Although incorporating systematically elicited WTP values from large samples into resource allocation processes has been postulated as best practice [9], there is no evidence that this has been done in any country or setting.

The need for priority setting tools is therefore clear and PBMA is a well-accepted tool, but there are challenges particularly with ongoing use and the input of the public. The study therefore aims to undertake a large scale PBMA whilst studying and addressing these concerns.

The chosen exemplar area for the study is National Health Service (NHS) dentistry in England. The spend on this is around £3.7 billion per year or 3.5% of the NHS budget [10]. Currently resource allocation is mostly based on historical allocations to individual dental practices or dentists. In addition, the standard contract with dental practices which stipulates what dentists should use this resource on is inflexible and not sensitive to demands from commissioners [11]. The case for more effective resource allocation was made strongly in an independent review of NHS dentistry [12].

Major changes in the commissioning of NHS care in England introduced as part of the Health and Social Care bill in 2009 took effect in April 2013. Essentially for dentistry, this meant that commissioning was removed from local bodies (Primary Care Trusts) to a national body (the National Commissioning Board, now referred to an NHS England) with part devolvement to local offices [10]. In order to be ready for the changes in April 2013, the board agreed to maintain a “steady state” initially, commissioning all services that had previously been commissioned. It has also committed to commissioning more intelligently as the new structure becomes more stable and there is some evidence that this is now beginning to happen [13]. As part of this more intelligent commissioning, the need to identify potential frameworks that commissioners can use to inform and make allocation decisions has been re- emphasised [10].

This research is therefore intended to apply PBMA to a national level programme (using dental services in England as the exemplar) incorporating the use of WTP values and to evaluate the process’s feasibility, utility and applicability from the perspective of the stakeholders involved.

## Methods/design

The aim of the study is to develop and use a framework which takes into account public values to inform resource allocation decisions to address the problem of scarce resources in health using NHS dentistry as an exemplar.

The study design is a mixed-methods study adopting a participatory action research (PAR) approach [14]. The design consists of two workstreams illustrated in Fig. 1; the first will involve participants undertaking a PBMA with the process continually evolving in response to the participants; the second will involve elicitation of societal preferences for different dental services being considered in WS1 using WTP from a representative sample of the public and then feeding the findings back into WS1.

**Fig. 1 Fig1:**
[figure not shown]
Overview of workstreams and Participatory Action Research

### Workstream 1 (WS1)

This will take place in three phases:I.pre-PBMA interviews with commissionersII.application and monitoring of the PBMA processIII.review of PBMA process

The success and failures will be studied using the principles of PAR, which studies a community’s response to (or actions in relation to) a problem or situation and involves the participants as co-researchers, drawing on a variety of evidence to reflect on the process undertaken. This project will particularly employ the participative and reflective elements of PAR [15].

### Sample

For Phase I, the sample will be drawn from the NHS England commissioners responsible for leading dental commissioning in sub-regional areas. For Phase II, the panel will be drawn from NHS England dental commissioners, dental professionals (in the form of Local Dental Network (LDN) chairs, who advise on commissioning), Consultants in Dental Public Health (CDPH) and patient/public representatives. For Phase III, a sub-sample of the panel and a sub-sample of WS2 participants (who were involved in the WTP survey) will be drawn. For all 3 phases, sampling will be purposive with the aim to ensure representation of different roles, different regions and different genders. For interviews and focus groups in all phases, the principle of saturation will be used to determine sample size.

### Recruitment

For Phase I, all dental lead commissioners will be contacted by email and invited to participate. For Phase II/III, the study will be explained during a commissioning seminar to be delivered to all dental lead commissioners and LDN chairs and those attending will be invited to participate. To recruit CDPHs, those previously involved in commissioning and priority setting work will be identified and approached by email. For patient/public representatives, an existing patient advisory group will be approached by speaking at one of their meetings. The participants for the public group in Phase III will be recruited by asking those completing the questionnaires in WS2 if they wish to be contacted about WS1. Those indicating they are interested will be approached on a selective basis in order to fulfil purposive requirements.

### Intervention: Phase I

The first phase will correspond with the “plan” stage of PAR.

Selected members of the panel will take part in semi-structured interviews which will focus on current areas of concern about the commissioning process in NHS dentistry as well as facilitators and barriers to making and implementing resource allocation decisions.

### Intervention: Phase II

The panel will then meet, facilitated by the research team, to tailor the PBMA process. The exact nature of the exercise will depend on the needs of the panel but the general principles will be consistent with the seven steps of micro-PBMA as outlined below [16].Determine the aim and scope of the priority setting exerciseCompile a “programme budget” The current resources used and activity information are identified.Form a “marginal analysis” advisory panelDetermine relevant decision-making criteria and weighting these e.g. maximising benefits, improving access and equity, etc., with reference to specified objectives of the health system and the community.Identify options for (a) service growth (b) resource release from gains in operational efficiency (c) resource release from scaling back or ceasing some servicesEvaluate investments and disinvestments in terms of costs and the criteria established in Step 4 and make recommendations for (a) funding growth areas with new resources (b) moving resources from 5(b) and 5(c) to 5(a).Validate results and reallocate resources

At the point of establishing options to be assessed in marginal analysis (Step 5), as well as continuing on through the ‘normal’ process of weighting criteria and assessing each option against these criteria, the options will be fed into WS2, in which each option will be assessed in terms of the mean societal value expressed as WTP. Once Step 6 is reached by the panel, the results of WS2 will be fed back into the process. WTP values for the programmes will be presented in a variety of ways and the panel will decide on what form of WTP presentation is most useful. The panel will also have to decide how much weight the WTP values will be given in any decisions made.

Phase II will correspond with the ‘Act & Observe’ phase of PAR which involve not only conducting the PBMA as outlined above but also collecting data and reflecting on the application of the framework, focusing on how the panel manage the process devised.

### Intervention: Phase III

Finally, the ‘Reflect’ phase of PAR corresponds to evaluation from participants relating their experiences, barriers, and successes. This evaluation will principally consist of another set of semi-structured interviews with panel members and two focus groups, one of the panel and one of members of the public (a sub-sample of those involved in WS2), which will focus on any differences in priorities. The results of this evaluation will be used to develop the framework further as a specific and original tool for dental decision-making, which can be improved further and adapted to other areas of health.

### Data collection and analysis

The data collected will be qualitative in nature and will consist of material gathered in interviews, focus groups and from field notes. The interviews and focus groups will be conducted using a topic guide which will evolve following each interview/focus group. The topic guide for Phase 1 has already been developed (Additional file 1) but further topic guides will be developed later in the project. Interviews and focus groups will be digitally recorded in audio and transcribed verbatim for analysis. The whole process will be observed and documented using field-notes during each stage, supplemented where necessary by audio-recordings and resultant transcripts. Analysis will follow the Framework Approach [17]. All data generated will be coded and analysed using the electronic database software NVivo.

### Workstream 2 (WS2)

This workstream consists of a set of surveys in which respondents are given descriptions of dental health care programmes competing for funds and are asked to rank them and then value them by stating a maximum WTP (through increased taxation per annum or voluntary contribution if the respondent does not pay tax). This approach to WTP is the most frequently used and will be referred to hereon as the standard approach. In addition to the standard approach, a new approach to eliciting WTP values which has been proposed to improve consistency, termed the ‘marginal’ or ‘incremental’ approach [18], will be trialled. The approach will be tested by randomly allocating respondents in one of the surveys to one of the two approaches, the hypothesis being that the new approach will lead to more consistent responses. The approach used for the remainder of the surveys will be determined by whichever approach proves to be more consistent and preferred is by the PBMA panel.

The surveys will be split across four waves spread over 4 months, with the same respondents being targeted at each wave. This will allow a large number of scenarios to be valued but also to allow ideas from WS1 to be fed in at various stages.

### Sample

The sample is designed to be representative of the population of England based on gender, age and socio-economic status. Where necessary, results will be weighted to account for differences in demographics of the sample versus the population. For pragmatic reasons, there will be an element of clustering of the sample based on geography.

As the data will be used for econometric modelling, sample size is dictated by the number required for sufficient power for regression models. The Events per Variable approach suggests a minimum of 10 cases per variable to be included in the regression model and with an estimated 15 variables per model and a splitting of the sample in 2 for some analysis (due to the methodological experiment), the minimum number is 300 [19]. In order to ensure a sample of 300 in the final wave, a larger sample will be required at each preceding wave, with previous experience suggesting attrition of 40% after Wave 1 and 15% after each of Waves 2 and 3 meaning an initial sample of 800 would be required. In addition previous experience suggests that certain groups are more likely to drop out so these will be oversampled in the first wave.

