### Recruitment

Interviewers will approach households in 50 clusters of randomly selected Lower Super Output Areas (LSOAs), by knocking on doors from a list of all addresses in the LSOA. Interviewers will recruit one person per household and use a quota target list to ensure selection of sufficient numbers of participants with required characteristics as outlined above to ensure a final representative sample.

An incentive in the form of £10 for completing wave 1 and then £15 for completion of waves 2, 3 and 4 will be offered. Those who are interested in the study will be given a verbal and written explanation by the interviewer.

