### Data analysis

As well as appropriate descriptive statistics (weighted where necessary for representativeness and ability to pay), the determinants of WTP will be determined using econometric analysis. The precise modelling will depend on the nature of the data but may include two-part models, tobits and Heckman Selection models. Appropriate sensitivity analysis will be performed.

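### The 50-area cluster design is missing from both the sample-size rationale and the named analyses; fitted as listed, these would give standard errors of mean WTP that are too small

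*Protocol article*

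**What the plan says.** All references are to Workstream 2 of the protocol article.

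- **Design.** The Sample section says that "there will be an element of clustering of the sample based on geography". The Recruitment section gives the number of areas: "Interviewers will approach households in 50 clusters of randomly selected Lower Super Output Areas (LSOAs". One person is recruited per household, to quotas.
- **Weights.** Groups expected to drop out more often are oversampled in the first wave. Where necessary, "results will be weighted to account for differences in demographics of the sample versus the population". The Data analysis section repeats the conditional weighting for descriptive statistics and adds ability to pay as a reason for it.
- **Sample size.** "The Events per Variable approach suggests a minimum of 10 cases per variable to be included in the regression model", "with an estimated 15 variables per model and a splitting of the sample in 2 for some analysis", which gives 300. The 300 is wanted in the last wave: "In order to ensure a sample of 300 in the final wave, a larger sample will be required at each preceding wave". Expected losses are "attrition of 40% after Wave 1 and 15% after each of Waves 2 and 3", and the starting sample is 800.
- **Where the split occurs.** The halving is attributed to the methodological experiment. Questionnaire design places the randomisation between standard and incremental elicitation in the first survey; one method is used afterwards.
- **Analysis.** Modelling depends on the data and "may include two-part models, tobits and Heckman Selection models". Clustering is not mentioned there, and no intracluster correlation, design effect or effective sample size appears anywhere.

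**The concern.** LSOAs are small areas, and people living in one tend to be socially alike. If WTP follows income, answers within an area will be correlated, and each further respondent from the same area adds less information than an independent one. A rule that counts heads then overstates the information available, and a tobit or two-part model fitted with ordinary standard errors overstates precision.

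The quantities most exposed are the mean WTP per programme, which the panel receives and decides how to weight, and the coefficients of covariates that vary mainly between areas, such as socio-economic status. Each respondent also values up to 8 programmes. If programmes were pooled in one model, that would be a second source of dependence.

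**Working it through.** **Inputs from the article:** 10 cases per variable; 15 variables; 2 halves; 50 areas; 800 at Wave 1; losses of 40%, 15% and 15%.

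**Inputs assumed, because the article gives none:** intracluster correlation (ICC) of 0.02, 0.05 or 0.10; coefficient of variation (CV) of the weights from 0 (no weighting loss) to 0.5.

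**1. The plan's own figures.** 10 x 15 x 2 = 300, reproduced exactly and with no design effect inside it. Retention to Wave 4 is 0.60 x 0.85 x 0.85 = 0.4335. So 300 / 0.4335 = 692.04, or 693 at the start, while 800 x 0.4335 = 346.8, about 347 at Wave 4. The 300 has no margin for clustering, but the 800 gives some: 346.8 / 300 = 1.156.

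**2. Formulas.** Design effect = [1 + (m - 1) x ICC] x (1 + CV²), where m is respondents per area. Effective n = n / design effect. The ratio of the true to the unadjusted standard error (SE) is the square root of the design effect. CV 0.5 contributes a factor of 1.25.

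**3. Standard error of an unadjusted Wave 1 mean** (m = 800/50 = 16, clustering only):

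| ICC | Design effect | Effective n | SE ratio |
|---|---|---|---|
| 0.02 | 1 + 15 x 0.02 = 1.30 | 615 | 1.14 |
| 0.05 | 1 + 15 x 0.05 = 1.75 | 457 | 1.32 |
| 0.10 | 1 + 15 x 0.10 = 2.50 | 320 | 1.58 |

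At Wave 4 with 346.8 respondents (m = 6.94), the SE ratios are 1.06, 1.14 and 1.26.

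**4. Effective cases per variable, in the analyses the article describes.** Randomisation is by participant, so a Wave 1 arm has 400 people and m = 8. The final wave is unsplit. Each cell is effective n / 15, first without a weighting loss and then with CV 0.5.

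| ICC | Wave 1, one arm (n 400, m 8) | Wave 4 at 300 (m 6) | Wave 4 at 346.8 (m 6.94) |
|---|---|---|---|
| 0.02 | 23.4 / 18.7 | 18.2 / 14.5 | 20.7 / 16.5 |
| 0.05 | 19.8 / 15.8 | 16.0 / 12.8 | 17.8 / 14.3 |
| 0.10 | 15.7 / 12.5 | 13.3 / 10.7 | 14.5 / 11.6 |

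The smallest entry is 300 / (1.50 x 1.25) = 160, and 160 / 15 = 10.7. Every cell is above 10.

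**5. Where a shortfall would appear.** If the final wave of 300 were itself halved, each half would have 150 people and m = 3. Without weighting loss this gives 150 / 1.04 / 15 = 9.6, 150 / 1.10 / 15 = 9.1 and 150 / 1.20 / 15 = 8.3. The article describes no such split. Outside the assumed range, ICC 0.10 with a weighting factor of 1.5 (in place of 1.25) gives 8.9 at 300 and 9.7 at 346.8, unsplit.

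**The case against.** A reader might infer that the sample is too small by the article's own rule, because 300 is exactly 10 x 15 x 2 and any design effect above 1 takes a half of it below 10. The documents do not support that. The halving belongs to the first survey, where 800 are planned, and later waves are analysed whole. The plan as a whole is not without slack either, since 800 yields about 347. This objection stands in full.

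A reader might also infer that the panel's ranking of programmes would be falsely precise. Each respondent values all the programmes in a survey, so comparisons between programmes are paired and shared area effects largely cancel. The randomised comparison of elicitation methods is likewise made within areas. This stands too: the inflation in step 3 applies to the level of a mean, not to these differences.

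Further points stand in part. Weighting is conditional, and oversampling likely drop-outs may even out the weights by the last wave. Income and other demographics, if entered in the models, would reduce the residual correlation. The article does not say that programmes will be pooled.

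Finally, the article leaves the modelling open and never says that standard errors will be unadjusted; a separate analysis plan may deal with this. That limits the concern to a conditional statement but does not remove it: the article fixes a sample size for a design that it declares clustered, mentions the weights, and leaves the clustering out of the calculation.

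**Conclusion.** The point holds in limited form. The sample-size rationale ignores the article's own cluster design, and the named analyses do not mention it. If they were run as listed, the true standard error of an unadjusted Wave 1 mean would be about 14%, 32% or 58% larger than reported at ICC 0.02, 0.05 or 0.10. The inflation is smaller at Wave 4, where areas hold about 7 people each. Coefficients of area-related covariates would be affected in the same direction; the article does not allow their size to be calculated.

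A breach of the 10-per-variable rule is not shown. Effective cases per variable stay between 10.7 and 23.4 at ICC 0.02 to 0.10 and weight CV up to 0.5. This result assumes equal numbers per area, weights unrelated to the outcome, and every respondent entering the model. The second part of a two-part model uses only positive WTP values, so its margin would be smaller by an amount that the article does not let one calculate.

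**What to change.** 1. State that WTP means and regression models will use survey-weighted estimation with standard errors clustered on LSOA.
2. If programmes are pooled in one model, cluster on LSOA, which also covers repeated values because respondents are nested in areas, or add a respondent random effect.
3. Restate the sample-size rationale with an assumed ICC and weighting effect. Report effective cases per variable for Wave 1 (split) and Wave 4 (unsplit), for the 800 already planned.

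The cost is a few sentences of analysis and sample-size text, standard software, and somewhat wider intervals. No extra recruitment is needed.
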